- 1. Analysis methods for safety endpoints

The type, severity, and incidence of adverse events and adverse reactions that occurred will be calculated and compared between the 2 groups.

- 1. Design of sample size

This study will be conducted for healthy volunteers as pilot positioning. Because the prior data do not exist, the scheduled number of registered subjects will be 30 subjects who are considered to be collectable within the specified study period.

1. Financing source and conflict of interest associated with the study

The study is sponsored by Abbott Japan Co., Ltd. and will be conducted by Yokohama City University as a contract research by Abbott Japan Co., Ltd.

Responsible person for study will declare any conflict of interest according to conflict of interest management rules of the study site.

The investigator will prepare the database to be used in this study by making it anonymous and Abbott Japan Co., Ltd. can neither access it nor perform statistical analysis using the database. Evaluation and interpretation of the results of the study will be performed by the investigator. The results of the study will not be disclosed unless the written consent is obtained according to the confidentiality rules.

1. Expenses on study participation

A research cooperation expenditure will be 50,000 yen per subject.

The investigator will purchase diclofenac sodium and study drug which will be used in the study.

1. Publication of the results

Whatever the study results may be, the principal investigator will publish the results in a scientific journal or in a scientific meeting.

Until 60 days prior to the publication of the study results, the investigator or the study site will submit the manuscript with the same contents to Abbott Japan Co., Ltd. to request their review and comments.

1. Study organization
   1. Responsible person for study (Investigator)

Department of Gastroenterology and Hepatology Yokohama City University Hospital
Professor   [name]

- 1. Sub-investigator

Department of Gastroenterology and Hepatology Yokohama City University Hospital
Postgraduate     [name]

Department of Gastroenterology and Hepatology Yokohama City University Hospital
Medical advisor   [name]

Department of Gastroenterology and Hepatology Yokohama City University Hospital
Postgraduate    [name]

Department of Biostatistics, Yokohama City University Graduate School of Medicine
Professor   [name]

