4.3.3　　At revision of the informed consent form

If the informed consent form is revised, the investigator, etc. should obtain the subject’s consent again.

1. Study drugs

Voltaren^®^ Tablets 25 mg (containing 25 mg of diclofenac sodium in 1 tablet)

Amitiza^®^ Capsules 24 µg (containing 24 µg of lubiprostone in 1 capsule)

1. Study design
   1. Study design

Open-label, randomized, parallel-group comparison study

For the first 6 subjects (3 subjects in each group) after the start of the study, the study treatment period or non-treatment period will be 28 days in this study. For the 7th subject and after that, the study treatment period or non-treatment period will be determined to be either 14 days or 28 days based on the results of the 6 subjects. If there is no difference in the 14-day treatment between the two groups but it is judged that there may be a tendency of difference in the 28-day treatment between the two groups, the study treatment period will be determined to be 28 days for the 7th subject and after that. In other cases, the study treatment period will be determined to be 14 days for the 7th subject and after that.

- 1. Dosage and administration of the study drug

Subjects will orally receive one capsule of Amitiza once daily after lunch for 14 days or 28 days.

- 1. Study registration

**This study will be registered to the UMIN Clinical Trials Registry and the information on the study will be made public. The clinical study registration will be done before registration of the first subject.**

- 1. Target sample size

35 subjects

- 1. Flow chart

*1: Lactulose/mannitol test, measurement of endotoxin activity in blood, intestinal flora test

*2: For the 7th subject and after that, the study treatment period (non-treatment period) will be determined to be either 14 days or 28 days based on the results of the first 6 subjects (3 subjects in each group).

Visit (1)

Visit (2)

Visit (3)

Study drug treatment group

Control group

Explain and obtain the consent

Medical examination, physical findings, etc.

Case registration

Administer diclofenac

Allocation

Tests for intestinal permeability^*1^

Tests for intestinal permeability^*1^

Administer the study drug

Not administer

←14 or 28 days*^2^→

7 days

←14 or 28 days*^2^→

Tests for intestinal permeability^*1^

Up to the first 6 subjects

Visit (1)

Visit (2)

Visit (3)

Visit (4)

Study drug treatment group

Control group

Explain and obtain the consent

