Medical examination, physical findings, etc.

Case registration

Tests for intestinal permeability^*1^

Administer diclofenac

Allocation

Tests for intestinal permeability^*1^

Administer the study drug

Not administer

Tests for intestinal permeability^*1^

Tests for intestinal permeability^*1^

Administer the study drug

Not administer

14 days

14 days

14 days

14 days

7 days

*1: Lactulose/mannitol test, measurement of endotoxin activity in blood, intestinal flora test

After 7th subject

- 1. Method of allocation

Until the 6th subject, block randomization is conducted using a block of block size 6. For the 7th subject and after that, block randomization is conducted using a block of block size 4.

- 1. Prohibited concomitant medications and therapies

After obtaining the consent until the completion of the study period, the use of proton pump inhibitors (PPIs), antibiotics, and intestinal drugs will be prohibited. However, the use of antibiotics will be allowed only for a local therapeutic purpose.

If the prohibited medication is used for inevitable reasons such as the treatment of adverse events, the investigator, etc. should describe the drug name, duration of use, intended use, etc. in the case report form.

1. Study implementation period

May 2015 - March 2016

1. Study method

This study will be implemented according to the following procedures and schedules.

- 1. Recruitment of subjects

The outline of this study will be posted on a bulletin board, etc. in the university to recruit subjects.

- 1. Study procedures

For the first 6 subjects (3 subjects in each group), the study treatment period or non-treatment period will be 28 days in this study. For the 7th subject and after that, the study treatment period or non-treatment period will be determined to be either 14 days or 28 days based on the results of the 6 subjects.

[Acquisition of consent]

- - - 1. The investigator, etc. will explain the contents of this study using the information document and obtain the written consent.
      2. After obtaining the consent, the investigator, etc. will perform medical interview, body measurements, etc. to judge the appropriateness of the subject’s participation.
      3. If the subject was judged to be eligible for participation, the subject will be registered. Also, the lactulose/mannitol test, measurement of endotoxin activity in blood, and intestinal flora test will be performed.

[Increase of intestinal permeability]

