- - - 1. Administer diclofenac sodium (75 mg/day) three times a day after every meal for 7 days.
      2. After administering diclofenac sodium for 7 days, the investigator, etc. will perform medical examination and allocate the subjects who can move to the study period to either a study drug treatment group or a control group.
      3. The lactulose/mannitol test, measurement of endotoxin activity in blood, and intestinal flora test will be performed.

For the first 6 subjects (3 subjects in each group) after the start of the study, the study treatment period or non-treatment period will be 28 days. For the 7th subject and after that, the study treatment period or non-treatment period will be determined to be either 14 days or 28 days based on the results of the 6 subjects.

[Up to the first 6 subjects]

[Study period]

(In the case of the study treatment group)

- - - 1. Administer 1 capsule of the study drug once a day after lunch for 14 days. The subjects are instructed to comply with the “Rules to be followed by subjects”.
      2. After administering the study drug for 14 days, the investigator, etc. will perform medical examination, as well as lactulose/mannitol test, measurement of endotoxin activity in blood, and intestinal flora test.
      3. Administer 1 capsule of the study drug once a day after lunch for 14 days.
      4. After administering the study drug for 14 days, the investigator, etc. will perform medical examination, as well as lactulose/mannitol test, measurement of endotoxin activity in blood, and intestinal flora test.

(In the case of the control group)

- - - 1. The study drug will not be administered (for 14 days). The subjects are instructed to comply with the “Rules to be followed by subjects”.
      2. After 14 days, the investigator, etc. will perform medical examination, as well as lactulose/mannitol test, measurement of endotoxin activity in blood, and intestinal flora test.
      3. The study drug will not be administered (for 14 days).
      4. After 14 days, the investigator, etc. will perform medical examination, as well as lactulose/mannitol test, measurement of endotoxin activity in blood, and intestinal flora test.

[After the 7th subject]

[Study period]

(In the case of the study treatment group)

- - - 1. Administer 1 capsule of the study drug once a day after lunch for 14 days or 28 days. The subjects are instructed to comply with the “Rules to be followed by subjects”.

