An unexpected adverse reaction is that which is not listed in the Interview Form of study drug (2014) or that which is listed in the Interview Form but its nature or severity is different from that described in the Interview Form.

- 1. Expected adverse reactions of study drug

Expected adverse reactions of Voltaren include the following events [based on the Interview Form of study drug (2015)].

Among the 1,474 subjects investigated until the approval, 239 adverse reactions were observed in 160 subjects (10.85%). Gastrointestinal symptoms such as gastric distress occurred in 139 subjects (9.43%) as major symptoms. Other symptoms included edema observed in 14 subjects (0.95%) and skin symptoms such as rash in 23 subjects (1.56%).

In the post-marketing drug-use result survey, 4,545 adverse reactions were observed in 2,749 (7.71%) out of the 35,653 subjects. As symptoms, gastrointestinal symptoms were observed in 2,365 subjects (6.63%) followed by general symptoms such as edema in 215 subjects (0.60%) and skin symptoms in 172 subjects (0.48%).

Reports of gastric ulcer and liver disorder as other adverse reactions accounted for below 0.1%.

Expected adverse reactions of Amitiza include the following events [based on the Interview Form of study drug (2014)].

Adverse reactions including abnormal laboratory findings were found in 196 (62%) /315 subjects who received study drug at a dose of 48 μg/day (24 μg b.i.d.) in 3 Japanese clinical studies. Most commonly observed adverse reactions included diarrhea in 95 subjects (30%) and nausea in 73 subjects (23%).

1. Study termination criteria in subjects

The study will be discontinued for the subject who meets any of the following criteria.

- - - 1. The subject himself offered to withdraw from the study participation
      2. The subject who could not comply with the prescribed administration of diclofenac sodium and study drug
      3. The subject for whom the prescribed test was not performed
      4. The subject who was judged impossible to move to the study period by the investigator, etc.
      5. The subject who turned out that he did not meet the inclusion criteria or violated the exclusion criteria after the start of the study
      6. The subject who developed an adverse reaction that falls under the category of Grade 2 or higher adverse reaction according to CTCAC v4.0 (moderate or severe prescribed in Section 11.6)

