- 1. Handling of personal data

For enrollment of a subject and preparation of his case report form, the investigator, etc. identify him by the subject identification code to retain the information as linkable anonymized data. Thus, personal data of a subject must be handled with caution.

1. Storage and destruction of records
   1. Storage of records

The investigator, etc. retains following records and documents for 5 years: case report forms, laboratory data, documents of ethical committee, documents on subject’s consent, documents on treatment with study drug and the study-related data.

- 1. Destruction of records

After completion of the storage period of records, the study-related data will be destroyed adequately, not to leak such secrets as personal data of subjects.

1. Statistical analysis

In this study, statistical analysis will be performed mainly for the following items. Details of the statistical design will be described in the statistical analysis plan.

- 1. Demographic characteristics

In addition to summary of subjects, summary statistics of demographic variables (including gender and age) of subjects will be shown.

- 1. Analysis set

Analysis set of the study will be Full analysis set (FAS) consisting of all subjects enrolled in the study, except for those described below.

• Subjects who were found to be ineligible for the study after the registration

• Subjects who took no study drug

• Subjects who had no efficacy data

- 1. Analysis methods for efficacy endpoints
     - 1. Primary endpoint

The summary statistics will be calculated for the permeability of the small intestine at baseline and after treatment respectively (mean, median).

For the primary analysis, (permeability of the small intestine after treatment - permeability of the small intestine at baseline) will be sought for each subject and the corresponding Wilcoxon test will be performed. The significance level will be 5% on both sides. For reference, the 2 groups will be compared using the Analysis of Covariance with permeability of the small intestine at baseline as a covariate.

- - - 1. Secondary endpoint

For endotoxin activities in blood and changes in the intestinal flora, too, (values after treatment - values at baseline) will be sought for each subject and the paired Wilcoxon test will be performed. The significance level will be 5% on both sides. For reference, the 2 groups will be compared using the Analysis of Covariance with baseline value as a covariate.

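### Open-label trial with printed fixed block sizes: up to about 31–32% of allocations can be known in advance, just when the investigator decides who moves on, and the post-diclofenac tests are listed after allocation

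*Protocol*

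**What the plan says.** - **Masking.** The protocol's Study design section describes an "Open-label, randomized, parallel-group comparison study". The control group receives nothing, so each allocation is visible once made.
- **Blocks.** Under Method of allocation: "Until the 6th subject, block randomization is conducted using a block of block size 6". Then: "For the 7th subject and after that, block randomization is conducted using a block of block size 4". The first block is split 3:3 ("For the first 6 subjects (3 subjects in each group) after the start of the study"). No ratio is stated for the later blocks, and no stratification is mentioned.
- **Allocation step.** Under Study procedures, in the part on increasing intestinal permeability, step 2 follows the 7 days of diclofenac. The investigator examines the subjects and is to "allocate the subjects who can move to the study period to either a study drug treatment group or a control group".
- **Tests.** Step 3 of the same list reads: "The lactulose/mannitol test, measurement of endotoxin activity in blood, and intestinal flora test will be performed". The protocol summary gives the same numbered order.
- **Discretion.** Study termination criteria in subjects includes: "The subject who was judged impossible to move to the study period by the investigator, etc".
- **Use of baseline.** Under Analysis methods for efficacy endpoints, the primary analysis is a Wilcoxon test on a difference: ("permeability of the small intestine after treatment - permeability of the small intestine at baseline) will be sought for each subject". ANCOVA with baseline as covariate is given for reference only. The text does not say whether baseline is the screening test or the post-diclofenac test.

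**The concern.** Randomisation protects the comparison only if nobody who decides on entry can foresee the next arm. Here three features meet. Past allocations are visible, the end of each block can be worked out from the printed sizes, and the person who allocates has just made a judgement call on whether the subject continues. A subject turned away at that point never enters an arm, so a later comparison of the arms cannot show it. With 30 or 35 subjects in all, one or two steered decisions could matter.

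The second issue is the order of the steps. If the post-diclofenac test is the baseline, it is listed after allocation, so subject and staff may know the arm when it is done. The assay is a laboratory measure, but fasting, conduct and timing of the test depend on people.

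**Working it through.** The protocol gives no figure for predictability, so there is none of its own to reproduce.

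**Inputs from the protocol.** Block of 6 (3:3) for subjects 1–6; blocks of 4 from subject 7. Total N is 35 under Target sample size and 30 under Design of sample size, so both are carried through.

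**Assumptions.** Later blocks are 2:2; there is one unstratified sequence; staff know all past allocations and the block size.

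**1. Allocations certain in advance, per block.** An allocation is certain once one arm of the block is full. Over all equally likely orders of a block of 2m, the expected number is 2m/(m+1).
- Block of 4 (6 orders): probability by position 0, 0, 1/3, 1. Sum 4/3 = 1.33, or 33.3% of 4.
- Block of 6 (20 orders): 0, 0, 0, 1/10, 2/5, 1. Sum 1.5, or 25.0% of 6.

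**2. Over the trial.**

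| | N = 30 | N = 35 |
|---|---|---|
| Subjects from no. 7 | 24 = 6 blocks of 4 | 29 = 7 blocks of 4, plus 1 |
| Certain, from no. 7 | 6 × 4/3 = 8.0 (33.3% of 24) | 7 × 4/3 + 0 = 9.33 (32.2% of 29) |
| Certain, whole trial | 8.0 + 1.5 = 9.5 (31.7%) | 9.33 + 1.5 = 10.83 (31.0%) |

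**3. Best guess (always name the less-filled arm).**
- Block of 4: 1/2 + 2/3 + 2/3 + 1 = 2.833 of 4 (70.8%). Block of 6: 4.1 of 6 (68.3%).
- N = 30: (4.1 + 6 × 2.833)/30 = 21.1/30 = 70.3%.
- N = 35: (4.1 + 7 × 2.833 + 0.5)/35 = 24.43/35 = 69.8%.
- Chance alone gives 50%.

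**4. After the change.** Block sizes from subject 7 were drawn at random in a simulation. Staff were assumed to know the set of sizes but not the draw.
- Sizes 4 and 6: about 6% of allocations certain.
- Sizes 4, 6 and 8: about 2–3% certain. Best-guess success is about 67%, against 70.8% (24 subjects) or 20.33/29 = 70.1% (29 subjects) with fixed blocks of 4.

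The 1.5 certain allocations in the first block of 6 stay as they are.

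**The case against.** **Predictability is not bias.** The percentages are an upper bound. They need staff who track the sequence and 1:1 blocks after subject 6, which the protocol does not state. Consent and registration come 7 days before allocation, so foreknowledge has little use at enrolment. Some stops before allocation are rule-based, such as non-compliance, missed tests or an adverse reaction of Grade 2 or higher. All of this stands, and it narrows the exposure to the discretionary move-on decision. It does not remove it, because that criterion is listed separately and rests on judgement.

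**Silence on concealment is not proof of its absence.** A biostatistics professor is on the study team, and the protocol does not say who holds the list. That stands too. But concealing the list does not help where block size and past allocations are known: the end of the block can be deduced without seeing the list.

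**Stronger readings that a reader might infer, and that the documents do not support:**
- *That baseline is the covariate of the primary analysis.* The primary analysis is a Wilcoxon test on the change; ANCOVA is for reference only. Baseline enters the primary analysis by subtraction.
- *That samples could be taken after the first dose.* The tests are listed before the heading under which dosing begins, and the section on investigations assigns them to the diclofenac period. Nothing describes late sampling.
- *That the flow chart confirms the order.* The chart is available only as loose text whose reading order is unreliable. The order rests on the numbered steps alone.
- *That baseline is certainly measured with the arm known.* Baseline is not defined. The screening test precedes allocation and would be unaffected, and the numbered list does not say when the arm is disclosed.

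**Conclusion.** The point holds as a design weakness that the protocol itself fixes, so it is not detail left to a statistical analysis plan. With printed fixed blocks in an open-label trial, up to 9.5 of 30 (31.7%) or 10.8 of 35 (31.0%) allocations are certain in advance, and a best guess is right about 70% of the time. This rests on 1:1 blocks, one sequence and staff who know past allocations. It means that foreknowledge could influence the move-on decision, not that it will.

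The second part is conditional. If baseline means the post-diclofenac test, which is the natural reading for a study of suppressing raised permeability, the value subtracted in the primary change score (and used in the reference ANCOVA) may be collected with the arm known. If baseline means the screening test, this part falls away and the first remains.

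The change is cheap and worth making. No effect on the trial's result has been shown.

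**What to change.** 1. From subject 7, use randomly ordered, undisclosed block sizes, for example 4, 6 and 8, from a list generated and held by the biostatistics department. Take the sizes out of the protocol that the investigators use.
2. At the post-diclofenac visit, record the move-on decision and complete the three tests before the allocation is opened.

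Both parts are needed. Recording the decision before the allocation is opened does not by itself remove predictability, since the next arm can still be guessed. Nor do mixed blocks remove it: they nearly abolish certain allocations (about 32–33% down to about 2–3% from subject 7), but best-guess success falls only from about 70% to about 67%.

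The cost is a new list and a changed order of steps within one visit. Final arm sizes may differ by a few subjects: stopping inside a block of 8 allows a difference of up to 4, against up to 2 with blocks of 4.

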- - - 1. Subjects take diclofenac sodium and study drug according to the instructions given by the investigator, etc.
      2. If a subject missed (could not) to take study drug after lunch, he/she takes it after supper. If he/she missed (could not) to take study drug after supper, he/she takes no study drug on that day.
      3. During the study period, combined treatments [medications (including supplements) and therapies] are prohibited, unless the investigator, etc. considers that use of combined treatment is necessary for treating adverse event(s) that occurred in a subject(s) during the course of the study.
      4. If a subject experienced any abnormality during the study period, he/she must inform the investigator, etc. of it.
      5. Any subject must not drink a large of alcohol during the study period.
      6. It is not allowed to take any food or drink from 21:00 onward on the day before and the day when lactulose/mannitol test is performed. However, a small amount of drink without sugar content is allowed.

1. Items and time points for investigations/examinations
   1. Patient characteristics

Investigation items: date of birth, gender, height, weight, complication, past medical history, history of allergy, concomitant drug, frequency of bowel movement, stool condition, with or without use of purgative

Target groups: study drug group, control group

Time points of investigation: Screening period

- 1. Vital signs

Investigation items: blood pressure, pulse rate

Target groups: study drug group, control group

Time points of investigation: screening period, at the time when an adverse event occurred, at the time of discontinuation

- 1. Physical findings

Investigation items: subjective or objective findings, adverse events, nausea, frequency of bowel movement, stool conditions

Target groups: study drug group, control group
Time points of investigation: screening period, period for treatment with diclofenac, period for treatment with study drug, at the time of discontinuation

- 1. Compliance to diclofenac

Investigation items: treatment period, daily dose, cessation/discontinuation of medication, reason of cessation/discontinuation of medication, reason for change

Target groups: study drug group, control group

Time points of investigation: Period for treatment with diclofenac

- 1. Compliance to study drug

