Investigation items: treatment period, daily dose, cessation/discontinuation of medication, reason of cessation/discontinuation of medication, reason for change

Target groups: Study drug treatment group

Time points of investigation: Period for treatment with study drug

- 1. Lactulose/mannitol test

Target groups: study drug group, control group

Time points of investigation: screening period, period for treatment with diclofenac, period for treatment with study drug, at the time of discontinuation

- 1. Endotoxin activity in blood

Target groups: study drug group, control group

Time points of investigation: screening period, period for treatment with diclofenac, period for treatment with study drug, at the time of discontinuation

Volume of blood to be collected: 2 mL in each time

- 1. Intestinal flora

Target groups: study drug group, control group

Time points of investigation: screening period, period for treatment with diclofenac, period for treatment with study drug, at the time of discontinuation

1. Endpoints
   1. Efficacy endpoints

Primary endpoint: Permeability of the small intestine using the lactulose/mannitol test

Secondary endpoints: endotoxin activity in blood, changes in intestinal flora

- 1. Safety endpoints

Adverse events, adverse reactions

1. Adverse events
   1. Adverse events

An adverse event is defined as any untoward medical occurrence (including abnormal laboratory findings) in a subject and which does not necessarily have to have a causal relationship with study drug. In this study, adverse events will be collected during the period from the start of treatment with diclofenac sodium to the end of treatment with study drug.

Adverse events will be assessed based on the clinical symptoms observed in subjects.

All adverse events will be documented by the investigator, etc. on the case report form to record the dates of its occurrence and resolution, its seriousness and severity, whether the subject was treated or not, its outcomes and the results of evaluation of causal relationship between the event and study drug.

- 1. Serious adverse events

A serious adverse event includes those described below.

- - - 1. Death
      2. Any adverse event which may lead to death
      3. Any adverse event which requires admission to a hospital or clinic, or prolongation of existing hospitalization (excluding hospitalization for routine tests)
      4. Disability
      5. Any adverse event which may result in disability

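### The adverse-event definition includes laboratory findings that nothing in the schedule looks for, and blood pressure and pulse after screening are taken only when an event or a discontinuation prompts them

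*Protocol*

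**What the plan says.** The safety endpoint in Section 10 (Endpoints) is "Adverse events, adverse reactions". Section 11.1 (Adverse events) defines the first of these: "An adverse event is defined as any untoward medical occurrence (including abnormal laboratory findings) in a subject". The next paragraph of that section gives the assessment rule: "Adverse events will be assessed based on the clinical symptoms observed in subjects".

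The tests behind the permeability visits are listed in the flow-chart footnote in Section 6: "1: Lactulose/mannitol test, measurement of endotoxin activity in blood, intestinal flora test". The only blood draw described is under endotoxin activity in Section 9: "Volume of blood to be collected: 2 mL in each time".

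For blood pressure and pulse, Section 9.2 (Vital signs) gives: "Time points of investigation: screening period, at the time when an adverse event occurred, at the time of discontinuation". Section 9.3 (Physical findings) is broader: "Investigation items: subjective or objective findings, adverse events, nausea, frequency of bowel movement, stool conditions". Those items are collected in both groups at screening, in the diclofenac period, in the study-drug period and at discontinuation.

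The safety analysis in Section 22 tabulates the type, severity and incidence of adverse events and adverse reactions and compares the two groups.

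**The concern.** Two things do not fit together.

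First, the definition admits laboratory abnormalities as events, but the assessment rule is symptom-based and the listed investigations include no haematology, biochemistry or urinalysis. A safety table built on the stated definition would show few or no laboratory events, and a reader could take that as reassurance when nobody had looked.

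Second, looking for an abnormal blood pressure or pulse after screening depends on what has already happened to the subject. The trial is open-label against no treatment, so symptoms, and the reporting of symptoms, may differ between groups. If they do, so does the intensity of looking, and the comparison of event types and severity carries part of that difference.

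**Working it through.** No figure in the Protocol has to be reproduced here. The check sets the definition, the measurement plan and the analysis side by side.

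**Laboratory findings**

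1. Definition (Section 11.1): laboratory abnormalities count as adverse events.
2. Assessment rule (Section 11.1): clinical symptoms.
3. Tests listed in Section 9, in the flow-chart footnote and in the row labels of the study schedule: lactulose/mannitol, endotoxin activity, intestinal flora. All three are efficacy measurements. There is no safety laboratory row.
4. Result: a symptomless laboratory abnormality has no planned route to detection in either group. The definition disagrees with both the rule and the schedule.

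**Blood pressure and pulse**

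1. Triggers in Section 9.2: screening (everyone), an adverse event, discontinuation.
2. Medical examinations planned after screening (Section 8): the first 6 subjects have one after diclofenac and one after each of two 14-day periods, so 3. From the 7th subject there is one after diclofenac and one at the end of the 14- or 28-day period, so 2.
3. Result for an event-free completer: a scheduled reading at 0 of 3 or 0 of 2 of these examinations.
4. The cell marks of the schedule table are not readable in the available text, so this result rests on the wording of Section 9.2.

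**Effect on the comparison**

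Let a group have n subjects, of whom x have at least one event, with E events in total. Suppose event-triggered readings add k vital-sign events among those x subjects.

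- Proportion with any event: x/n before and x/n after, because each of these subjects is already counted.
- Number of events: E before and E + k after.
- Types and worst severity: can change in those x subjects.

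The event trigger therefore leaves overall subject-level incidence alone but can move event counts, event types and severity. A reading prompted by discontinuation in a subject without an event could in principle add a subject to x. That is a small exception.

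**The cited reaction rate**

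Section 11.7 states: "Adverse reactions including abnormal laboratory findings were found in 196 (62%) /315 subjects who received study drug at a dose of 48 μg/day". The arithmetic is right (196/315 = 62.2%). The figure includes laboratory findings and comes from 48 μg/day, against one 24 μg capsule a day here (48/24 = 2). It does not describe what this trial would record.

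**The case against.** The best defence is that the parenthesis on laboratory findings is generic definition wording, and that the symptom-based rule in the same section already says how events are measured here. Vital signs are not named in the safety endpoint, and a reading taken at an event can be seen as part of working up that event. Symptoms and objective findings are collected in both groups in every period. The Protocol plans no laboratory-safety claim and no comparison with the 62% figure. This is a small pilot with permeability as its primary endpoint.

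Much of this stands. The symptom-based core of the endpoint is scheduled equally in both groups, and the laboratory gap is the same in both. What it does not answer is that Section 11.1 still gives a definition and a rule that disagree. Nor does it answer that an abnormal reading could be recorded as an untoward occurrence although readings are not sought equally.

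Three stronger readings are tempting and are not supported:

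- A reader might infer that laboratory abnormalities can never be recorded. Section 11.3 provides for medical work-up of events, which could reveal one. What is missing is systematic ascertainment.
- A reader might infer that vital signs are retaken only in subjects who report harm. Discontinuation also triggers them, and Section 12 includes reasons unrelated to harm, such as withdrawal by choice or a missed test.
- A reader might try to size an excess of rechecks in the lubiprostone group from the 62% rate. The documents give no control rate, and the 62% is not comparable, so no ratio can be derived. Events in the diclofenac period, before allocation, would also trigger readings in both groups.

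**Conclusion.** The point holds as an inconsistency in the safety definition together with outcome-dependent measurement of blood pressure and pulse. Laboratory abnormalities are not systematically ascertained in either group. Vital-sign abnormalities after screening would be found mainly in subjects who already have an event, which can affect the types, severity and number of events compared, but not the proportion of subjects with any event.

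The direction of any imbalance depends on which group has more events. The Protocol expects diarrhea and nausea with lubiprostone, so more readings in that group are plausible, but the size cannot be estimated from the documents.

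The conclusion assumes that Section 9.2 is the complete list of vital-sign time points and that an abnormal reading may be recorded as an event. It is a modest defect that is cheap to correct. It belongs in the Protocol because an analysis plan cannot recover readings that were never taken.

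**What to change.** 1. In Sections 10 and 11.1, state that the safety endpoint is symptomatic adverse events. Add that laboratory abnormalities are not systematically ascertained, so their absence supports no conclusion about laboratory safety.
2. Record blood pressure and pulse in both groups at the medical examinations already planned after diclofenac and at each study-period visit, and say whether an abnormal reading counts as an event. Otherwise, leave event-triggered vital-sign findings out of the between-group comparison in Section 22.
3. Reconcile the discontinuation time point in Section 9.2 with the closing sentence of Section 12, which says that tests after discontinuation are not done as a rule. It is unclear whether that covers vital signs.

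Cost: no new visit and no blood test. If everyone completes, the extra readings number 6 × 3 + 24 × 2 = 66 with the 30 subjects in the sample-size section, or 6 × 3 + 29 × 2 = 76 with the 35 in the summary, at a few minutes each. The safety claim becomes narrower.
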